### Recruitment

The patients are recruited from the outpatient HF clinic of Hospital de Clínicas de Porto Alegre. The recruitment period for the study is planned to range from October 2017 to July 2020. Eligible patients are informed of the study and invited to participate; those who accept are tested by a blinded assessor and randomly allocated to one of the study groups. A flow diagram of the patient recruitment process is shown in Fig. 2.

### Assignment of interventions and blinding

Group allocation was determined by eight blocks of 4 individuals (Software Rx64 version 3.1.1) in a 1:1 ratio generated by an external researcher. The investigator in charge of randomization does not participate in the other data collection stages. Allocation concealment is implemented through a central randomization routine conducted by investigators with access to the randomized list and the investigator charged with requesting the code to place subjects in the intervention group. In brief, the assigner contacted the external researcher to request whenever one or more subjects should enter an intervention arm. Thereafter, the external researcher will consult the code in consecutive order and uncover the code relative to the requested subject(s). Such requests will be documented and archived for further accountability. To ensure intervention blinding, communication with participants is not performed by the investigators involved in the outcome assessments.

Due to the nature of the interventions, the researcher conducting the exercise sessions as well as participants are not blinded. To ensure assessor masking, the subjects are asked to omit their assigned group and not to talk about their interventions during the outcome evaluation sessions. In the case of unintentional unblinding for any reason, the involved researcher will notify the principal researcher. In such cases, participant ID, date, and unblinding circumstances will be documented for internal control.

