### Sample size

Our sample size calculation was based on Feiereisen et al., who enrolled subjects with HF with reduced ejection fraction to assess the effect of strength in comparison with aerobic and combined aerobic-strength training on their peak VO_2_ [31]. Considering a power of 80%, a significance level of 5% and an effect size of 0.2 for the peak VO_2_, a total sample size of 32 subjects was estimated, including 16 in each study group. To account for a 20% estimated participant loss or refusal rate, we defined that 19 patients should be enrolled in each group, totalizing 38 subjects.

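### The randomisation list as described holds 32 codes for a planned 38 patients, so no allocation code or concealment procedure is documented for patients 33 to 38

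*Protocol article*

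**What the plan says.** Two sections of the protocol article bear on the number of codes.

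- **Sample size.** The calculation ends with "a total sample size of 32 subjects was estimated, including 16 in each study group". The text then inflates this: "To account for a 20% estimated participant loss or refusal rate", "we defined that 19 patients should be enrolled in each group, totalizing 38 subjects".
- **Assignment of interventions and blinding.** "Group allocation was determined by eight blocks of 4 individuals", "in a 1:1 ratio generated by an external researcher". Codes are held by that external researcher and released on request, in list order, and each request is documented and archived. The same section gives one block size only, and says that "the researcher conducting the exercise sessions as well as participants are not blinded".

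No section mentions a longer list, a second list or a rule for extending the first. The Abstract describes the trial as recruiting since October 2017, and the Recruitment section plans recruitment until July 2020.

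**The concern.** A list that runs out before enrolment is complete leaves the remaining allocations to a procedure that nobody has written down. Here the list appears to have been sized on the figure before inflation, and the loss allowance was added to the recruitment target but not to the list.

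Two things are at stake. If recruitment ends when the codes end, the trial loses the margin it planned for dropout, and in a trial of this size that margin is a large part of the information. If recruitment continues to 38, a reader of the article cannot tell how the last six patients were allocated or whether the assignment was concealed. Allocation cannot be repaired once patients have entered, so this should be settled before the list is exhausted.

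A lesser matter concerns the same list. A single block size, stated in print, for a single-centre trial in which treatments are visible, makes some assignments inferable under certain conditions.

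**Working it through.** **Inputs** (protocol article): 8 blocks of 4, ratio 1:1 (Assignment of interventions and blinding); 32 patients before loss, 16 per group; loss or refusal 20%; 38 patients to be enrolled, 19 per group (all Sample size).

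**1. Reproducing the planned enrolment.** Multiplying by one plus the loss rate: 16 x 1.2 = 19.2, rounded to 19 per group, and 2 x 19 = 38. This matches the stated figure. Dividing by the retained fraction, which is the usual formula, gives 32 / (1 - 0.20) = 40. The difference of two patients is minor and is not the point here.

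**2. Codes on the list.** 8 x 4 = 32, which is the figure before inflation.

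**3. Shortfall.** 38 - 32 = 6 codes; 6 / 38 = 15.8% of planned enrolment.

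**4. Consequence if recruitment stops with the list.** Expected completers at 20% loss:

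| Patients allocated | Calculation | Completers |
|---|---|---|
| 32 (list as written) | 32 x 0.80 = 25.6 | about 26 |
| 38 (planned) | 38 x 0.80 = 30.4 | about 30 |
| Target | | 32 |

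**5. Length of list needed.** 38 / 4 = 9.5. Nine blocks of 4 give 36 codes, still 2 short; ten give 40. If recruitment stops at 38 with the tenth block half used, the first two codes of that block may fall in the same arm, and the trial then ends 20:18 instead of 19:19. Six codes made up of complete balanced blocks (for example one of 4 and one of 2) after 32 balanced codes give 19:19.

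**6. Predictability within blocks of 4.** A 1:1 block of 4 has six orderings. In AABB and BBAA the third and fourth assignments are fixed by the earlier ones (2 each). In ABAB, ABBA, BABA and BAAB only the fourth is fixed (1 each). In total (2 x 2 + 4 x 1) / (6 x 4) = 8 / 24 = 33.3%, or 1.33 per block and about 10.7 of 32. Guessing the arm that is behind in the block, and at random when the arms are level, is right with probability 1/2, 2/3, 2/3 and 1 at the four positions, a mean of 70.8% against 50% under simple randomisation. These figures hold only if codes are released one at a time to someone who knows all earlier assignments and where each block starts.

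**The case against.** The strongest defence is that the external researcher can simply add blocks under the same procedure, and that a condensed article need not say so. The first half stands: nothing in the text prevents an extension, and that is also the remedy. The second half does not, because the article does not leave the list length open. It states a length and an enrolment figure, and the two conflict.

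A second defence is that the allowance covers refusals before randomisation, so that 38 approached patients would yield 32 allocated. The wording on loss or refusal gives this some colour. But the text goes on to fix 19 patients in each group, and a patient belongs to a group only after allocation. Thirty-eight enrolled by group means 38 allocations.

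Three stronger readings are tempting, and the documents do not support them.

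- *A reader might infer that the last six patients are allocated without concealment.* The article is silent on them. It describes a standing central procedure that could cover them.
- *A reader might infer that one third of assignments are known in advance and that enrolment is selective.* One third is a ceiling under the conditions in step 6 of the working. The article does not say that the person requesting codes knows the earlier assignments or decides eligibility. The investigator in charge of randomisation takes no part in the other data collection stages; consent and baseline testing come before allocation, which narrows the room for selection without removing it; and one request may cover several patients, whose codes cannot be predicted from one another.
- *A reader might think it an error that 38 is not a multiple of 4.* It is not. A list may be longer than enrolment and end in a partly used block, at a cost of 20:18 at worst.

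**Conclusion.** The point holds as a mismatch between two stated figures. The list described has 32 codes, planned enrolment is 38, and codes for six patients (15.8%) are not documented. This rests on arithmetic and on reading the per-group enrolment figure as allocated patients; it needs no outside assumption.

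The figure of about 26 completers is conditional. It assumes that recruitment stops when the list ends and that loss is the 20% the protocol allows for.

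The single published block size is a secondary risk. It is not evidence that anyone has anticipated or steered an assignment.

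**What to change.** **Main change.** Before code 32 is used, the same external researcher generates and archives a continuation list that covers the full planned enrolment, with the same central release in list order. The section on assignment of interventions is then amended to state the full list length. The statement of eight blocks may be an accurate record of the list first generated; if so, it should be supplemented and not overwritten. If the list has already been extended, the sponsor should state how and when.

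**Secondary option.** For codes not yet released, use varying block sizes and withhold them from the person who requests codes. Withholding matters more than the particular sizes, since small blocks are themselves predictable once known. This does nothing for codes already released, and in a continuation of only six codes the gain is small.

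**Cost.** About an hour of the external researcher's time and a documented amendment, with at most a small arm imbalance such as 20:18.

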### Data collection

Standard operating procedure documents are available for each assessment. The outcome assessors were trained and the handling of a standard operating procedure short version is mandatory during each data collection period. All variables will be assessed at baseline (prior to randomization) and at study completion.

### Statistical analysis

The characterization of the sample will be performed by descriptive statistical analysis using measures of central tendency (mean and median) and variability (standard deviation and interquartile range). The normality of the data will be tested by the Shapiro-Wilk test. Intra- and inter-group analyses will be performed before and after the total 12-week intervention period. For both analyses the generalized estimation equations (GEE) will be used. Correlations between peak VO_2_ and study variables – quality of life, functionality, muscle strength, endothelial function, and lean body mass – will be examined by Pearson or Spearman coefficients as appropriate.

In all tests, a significance level of *p* < 0.05 will be adopted. All data will be analyzed using SPSS Statistics for Windows version 20.0 (IBM Corp., Armonk, NY, USA) by the intention-to-treat and protocol methods.

Dropouts (essentially, participants who withdraw consent for continued follow-up) or missing data will be included in the analysis by modern imputation methods.

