**Methods:**

This randomized parallel-design examiner-blinded clinical trial includes individuals of both sexes aged ≥40 years receiving regular follow-up at a single academic hospital. Subjects will be randomly allocated to an intervention group (for 12-week functional training) or an active comparator group (for 12-week strength training). The primary outcomes will be the difference from baseline to the 3-month time point in peak oxygen consumption on cardiopulmonary exercise testing and quality of life assessed by the Minnesota Living with Heart Failure Questionnaire. Secondary outcome measures will include functionality assessed by the Duke Activity Status Index and gait speed test; peripheral and inspiratory muscular strength, assessed by hand grip and manovacuometry testing, respectively; endothelial function by brachial artery flow-mediated dilation; lean body mass by arm muscle circumference; and participant adherence to the exercise programs classified as a percentage of the prescribed exercise dose.

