**Fig. 1 Fig1:**
[figure not shown]
Examples of functional exercises. Legend: 1, run on trampoline; 2 (a, b), Swiss ball wall squat; 3, overhead press with dumbbells; 4 (a, b), plank and variation; 5, squat on rigid balance board; 6 (a, b), oblique twist with elastic band; 7, agility on ladder drills; 8 (a, b), reverse plank

The method aims to improve the functional capacity of the individual using exercises that relate to his specific physical activity, effectively transferring gains to one’s daily life [14, 17]. In fact, functional training, sometimes called neuromotor exercise training, is a recommendation of the American College of Sports Medicine for apparently healthy adults of all ages [18]. Functional training could improve peak VO_2_ since it also includes an aerobic component. However, some aspects such as volume, performance patterns, and progression remain unknown. Additionally, the effectiveness of exercise training in chronic diseases has not been established [14]. The choice of the strength group as an active comparator group was because this type of training does not increase peak VO_2_ in the same magnitude as exercises with a larger cardiopulmonary component, as we expect in functional training. The primary objective of the present study is to compare the effects of functional training versus strength training on the cardiopulmonary exercise capacity and quality of life of patients with HF. Secondary objectives are to evaluate the: (1) effects of functional training versus strength training on functionality, muscle strength, endothelial function, and lean body mass; (2) adherence of participants to both physical training protocols; and (3) safety of a functional training program.

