**Fig. 2 Fig2:**
[figure not shown]
Proposed trial design

Patients’ baseline demographic and clinical information including age, sex, HF etiology, left ventricle ejection fraction, and NYHA functional class are obtained from their electronic health records.

The primary outcome measures are cardiopulmonary exercise capacity and quality of life; the secondary outcomes include assessment of functionality, peripheral and inspiratory muscle strength, endothelial function, lean body mass, and participant adherence to exercise programs.

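### Two equal primary outcomes, each tested at p < 0.05 in two analysis sets, have no success rule and no leading set; if either outcome suffices, the family-wise error is about 8–10%

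*Protocol article*

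**What the plan says.** The Abstract gives the primary outcomes as "the difference from baseline to the 3-month time point in peak oxygen consumption on cardiopulmonary exercise testing and quality of life". The Outcomes section repeats this: "The primary outcome measures are cardiopulmonary exercise capacity and quality of life". The Background states a single primary objective, "to compare the effects of functional training versus strength training on the cardiopulmonary exercise capacity and quality of life of patients with HF". None of these places ranks the two outcomes.

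The Statistical analysis section sets the level for every test: "In all tests, a significance level of *p* < 0.05 will be adopted". It plans comparisons within and between groups ("Intra- and inter-group analyses will be performed before and after the total 12-week intervention period") and analyses the data "by the intention-to-treat and protocol methods". It does not say which of the two analyses carries the conclusion, in what order the outcomes are tested, or whether one or both must be significant.

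The Sample size section states 80% power and a 5% significance level for peak VO2 only: 16 evaluable patients per group, 38 enrolled in total. It does not say that this makes peak VO2 the leading outcome.

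**The concern.** With two primary outcomes, the meaning of a positive trial depends on the success rule. If either outcome can carry the claim and each is tested at the full 5%, the chance of at least one false positive exceeds 5%. Adding a second analysis set with no stated role opens further routes to a claim.

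If both outcomes must succeed, the type I error is not inflated, but the probability of success is lower than the power for either outcome alone. Only peak VO2 was sized.

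As the text stands, the authors could choose between these readings after seeing the results. A trial that failed on peak VO2 could report a positive primary result on the questionnaire alone, or in the protocol set alone, without departing from anything written.

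**Working it through.** **Inputs from the article.** Two primary outcomes (Abstract, Outcomes); 0.05 per test (Statistical analysis); two analysis sets (Statistical analysis); 80% power for peak VO2 (Sample size).

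**Assumptions, because the article gives no figure.** Tests are two-sided. The two test statistics are bivariate normal with correlation ρ between 0 and 0.8. Where the second set is counted, the protocol set holds 80–90% of patients. Where both outcomes must succeed, the Minnesota score also has 80% power.

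**The plan's own figures.** The 5% is a per-test level, and each test taken alone has that error. The 80% is a marginal power for peak VO2. The Sample size inputs do not by themselves determine the 32 patients. They give 32 if the effect size of 0.2 is read as Cohen's f for a group-by-time interaction with a before–after correlation of about 0.7, which is not stated (power 80.7% at 32). The error calculation below does not depend on that reading.

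**Case A: either outcome suffices, one analysis set.** For independent outcomes the error is 1 − (1 − 0.05)² = 1 − 0.9025 = 0.0975. In general it is 1 − P(|Z1| < 1.96 and |Z2| < 1.96).

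| ρ | 0 | 0.3 | 0.5 | 0.7 | 0.8 |
|---|---|---|---|---|---|
| Family-wise error | 9.75% | 9.5% | 9.1% | 8.3% | 7.8% |

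**Case B: either outcome in either set suffices.** The sets are nested, so the two results for one outcome are taken to correlate at the square root of the protocol fraction (√0.9 or √0.8). Simulation with 2,000,000 draws:

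| ρ | Protocol set 90% | Protocol set 80% |
|---|---|---|
| 0 | 12.5% | 13.7% |
| 0.5 | 11.7% | 12.7% |
| 0.7 | 10.7% | 11.7% |

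**Case C: both outcomes must succeed, one set.** When neither outcome has an effect, the error is 0.05 × 0.05 = 0.25% at ρ = 0 and about 1.7% at ρ = 0.7. When only one has an effect, it is at most 5%. The error is therefore controlled. Power for success, with 80% on each outcome, is 0.8 × 0.8 = 0.64 at ρ = 0 and rises with correlation:

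| ρ | 0 | 0.3 | 0.5 | 0.7 | 0.8 |
|---|---|---|---|---|---|
| Power for both | 64% | 67% | 69% | 71% | 73% |

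**Possible rules.** A fixed sequence in one named set keeps the error at or below 5% with each test at 0.05. Splitting the level equally (0.025 each) gives 1 − 0.975² = 4.94% at ρ = 0 and 4.65% at ρ = 0.5. Under the Cohen's f reading above, the split lowers peak VO2 power at 32 patients from 80.7% to 71.1%, and 40 evaluable patients are needed instead of 32.

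**The case against.** The strongest reply is that the article nowhere says either outcome is enough. Its primary objective joins the two with a conjunction, which can be read as requiring both, and under that rule testing each at 5% is correct. A reader might infer that the plan's error rate is in fact nearly double its stated 5%. The text does not support that as an unconditional statement: the inflation belongs to one of two open readings.

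A reader might also infer that the plan misstates its error or its power. It does not. The 5% is stated per test and no overall rate is claimed. The 80% is stated for peak VO2, and neither success rule changes that marginal figure.

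A further reply is that testing order and the roles of analysis sets are often left to an analysis plan, which is not shown here. A fixed sequence would even be compatible with the p < 0.05 sentence. This has weight, but the article is not silent. It fixes the unadjusted level for every test, without qualification, over two equal primaries and two sets, so following it literally leaves every route to a claim open.

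Finally, the Assignment of interventions and blinding section says that "the researcher conducting the exercise sessions as well as participants are not blinded", and the questionnaire is self-reported. It is tempting to count this as part of the same defect. It is a separate question of bias: the article discloses it, both arms receive supervised exercise of the same length, and a testing order would not remove it.

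**Conclusion.** The point holds in conditional form. The article leaves open the success rule for two equal primary outcomes and the leading analysis set, while giving every test the full 5%. If either outcome suffices, the family-wise error is about 8–10% in one set over correlations from 0 to 0.8, and about 11–14% if either set counts (correlations 0 to 0.7). If both are required, the error is controlled and the power for success is about 64–73%.

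The ranges rest on assumed correlations and an assumed size of the protocol set. The power range also rests on 80% power for the Minnesota score, for which the article offers no basis. The missing rule is established from the text; which reading the investigators intend is not. This should be fixed, but it does not by itself invalidate the design.

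**What to change.** Before data are analysed, add to the Statistical analysis section:

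- The intention-to-treat analysis is primary. The protocol analysis is a sensitivity analysis and cannot by itself support a claim.
- The between-group comparison of peak VO2, the outcome the trial was sized on, is tested first at two-sided 5%.
- The Minnesota score is tested at two-sided 5% only if peak VO2 is significant. Otherwise it is reported as an estimate with a 95% confidence interval.

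The cost is a few sentences, with no extra patients and no loss of power for peak VO2. The downside is that quality of life cannot be claimed on its own if peak VO2 fails.

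If the investigators want the two outcomes to keep equal standing, they can require both, and state the power for that, or split the level, and accept the loss of power or the larger sample shown above. Either also controls the error. The rule has to be written down beforehand, because an order chosen after the results are known does not control it.

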### Monitoring

#### Data monitoring

The study does not have a data monitoring committee. We reason that this committee would not be mandatory due to the characteristics of the interventions and outcomes despite the trial’s high overall quality.

#### Harms

The study will monitor for the following physical training-related adverse effects during the intervention period: shortness of breath, fatigue, and muscular pain. The researcher responsible for the intervention will identify possible solutions for any adverse effects.

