#### Criteria for discontinuation and safety interventions

A participant may be discontinued from the study at the investigator’s discretion for safety reasons. For any study subjects, an incident cardiovascular event, hospitalization, or severe health event during the intervention period are considered criteria to discontinue study participation. If typical thoracic pain, disabling dyspnea, and/or exercise-related syncope occur during the training session, the exercise intervention will be interrupted. Trained nursing staff at the clinical research center will provide clinical assessment and event-directed interventions accordingly. If necessary, immediate transfer to the hospital’s emergency department will be performed.

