#### Strategies for trial retention

During weekends, participants allocated to both groups receive phone calls to reinforce intervention session time and place. We use phone calls to inquire about any adverse events if a participant misses a session of any intervention arm. The phone call schedule will cease for participants declaring their withdrawal from the study.

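### Safety of functional training is a stated objective without a matching outcome, and the described capture of harms beyond three listed symptoms depends partly on missed sessions

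*Protocol article*

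**What the plan says.** In the Background, the third secondary objective is "3) safety of a functional training program". The Outcomes section then states that "the secondary outcomes include assessment of functionality, peripheral and inspiratory muscle strength, endothelial function, lean body mass, and participant adherence to exercise programs". The Abstract gives a similar list, again without a safety item, and the Statistical analysis section does not mention adverse events.

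Harms are dealt with in three other places:

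- **Harms:** "The study will monitor for the following physical training-related adverse effects during the intervention period: shortness of breath, fatigue, and muscular pain". It adds: "The researcher responsible for the intervention will identify possible solutions for any adverse effects".
- **Criteria for discontinuation and safety interventions:** "an incident cardiovascular event, hospitalization, or severe health event during the intervention period are considered criteria to discontinue study participation". It also states: "If typical thoracic pain, disabling dyspnea, and/or exercise-related syncope occur during the training session, the exercise intervention will be interrupted".
- **Strategies for trial retention:** "We use phone calls to inquire about any adverse events if a participant misses a session of any intervention arm".

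**The concern.** The first two secondary objectives, on function and on adherence, each have named outcomes. The safety objective has none. What stands in its place is a list of three symptoms that are expected with exertion and that overlap with heart failure itself. The Background describes progressive fatigue as part of the disease, and the discontinuation section treats disabling dyspnea as a reason to interrupt exercise.

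The events on which a safety statement would turn are not tied to the objective. Serious events act as triggers for stopping. Open questioning is described only for participants who were absent.

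This matters because the Discussion presents the trial as the first of functional training in heart failure, so readers will look to it for safety information. The programme includes trampoline running, a balance board and ladder drills, in patients with an ejection fraction of 45% or less. Falls and musculoskeletal injuries are foreseeable, yet neither is named.

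**Working it through.** The protocol states no safety event rate, safety power or other safety figure, so there is none to reproduce. The check is a comparison of sections, followed by two short calculations.

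**1. Objectives against outcomes**

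| Secondary objective (Background) | Matching outcome (Outcomes section) |
|---|---|
| 1: functionality, strength, endothelial function, lean mass | all listed |
| 2: adherence | listed |
| 3: safety of functional training | none |

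**2. Routes by which an event would come to notice, as described**

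- Route A: the three symptoms in the Harms section, during the intervention period.
- Route B: the discontinuation and interruption triggers.
- Route C: the phone call after a missed session, open to any adverse event, in both arms.

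| Event | A | B | C |
|---|---|---|---|
| Breathlessness, fatigue, muscle pain | yes | only if disabling dyspnea in a session, or severe | if a session is missed |
| Cardiovascular event, hospitalization | no | yes | if a session is missed |
| Chest pain or syncope in a session | no | yes | if a session is missed |
| Fall or joint injury, session missed | no | only if severe | yes |
| Fall or joint injury, not severe, attendance continues | no | no | no |

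The last row is the gap. Route B brings serious events to notice, but the protocol does not say that they are counted or compared by arm.

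**3. How far open inquiry depends on attendance**

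Inputs: 36 sessions (Intervention) and an adherence threshold of 80% (Adherence). Assume one call per missed session.

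- Sessions needed to be adherent: 0.80 × 36 = 28.8, so 29.
- Missed sessions possible for an adherent participant: 36 − 29 = 7.
- Open inquiries under the described rule: 0 with full attendance, up to 7 for an adherent participant, 8 or more for a non-adherent one.
- With one open question per scheduled session, in person or by phone after an absence: 36 for each participant who completes the programme.

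Adherence is itself an outcome to be assessed in both arms. If it differs, the amount of open inquiry differs with it. The protocol does not say that it will differ.

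**4. What the sample size allows (context only)**

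Input: 19 enrolled per arm, from 16 before allowance for loss (Sample size).

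- One-sided 95% upper limit with no events: 1 − 0.05^(1/n), which is 14.6% for n = 19 and 17.1% for n = 16.
- Chance of at least one event among 19: 1 − (1 − p)^19. For assumed true risks of 1%, 2%, 5% and 10% this is 17%, 32%, 62% and 86%.
- Power to detect an assumed 5% against 20% with 19 per arm: about 28%.

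These figures describe the sample size and would be the same with perfect recording. They show that any safety result here is descriptive. They are not evidence that events are undercounted.

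**The case against.** The strongest reply is that harms are better covered than the Harms section alone suggests. Every session is supervised by a physiotherapist, with heart rate and blood pressure measured before and after. The discontinuation section names serious events and provides for nursing assessment. The missed-session call applies to both arms, and it is a procedure for people who cannot be asked in person; it does not say that those present go unasked. The outcome list is introduced as including its items, so it is not expressly closed. Adverse event forms may exist in a fuller protocol, and their absence from an article is no fault.

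Much of this stands, and it limits the point. Three stronger readings are tempting, and the protocol supports none of them:

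- A reader might infer that monitoring covers only three harms. The Harms section names only three, but the other two sections bring further events to notice.
- A reader might infer that unblinded staff decide what counts as training-related. It is stated that "the researcher conducting the exercise sessions as well as participants are not blinded", and the researcher responsible for the intervention deals with adverse effects. But that describes management, and no section assigns attribution.
- A reader might infer that the trial can say nothing about safety. A limited descriptive statement is possible if the events are recorded and reported by arm.

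What the reply does not answer is the mismatch in the text itself: an objective without an outcome, a specified symptom list, and an open inquiry whose only described trigger is absence. Supervision makes it likely that an event during a session is seen. It does not ensure that an event between sessions is asked about.

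**Conclusion.** The point holds in a limited form. The safety objective has no named outcome, and the sections that deal with harms are not connected to it. Followed as written, the plan would probably bring serious events to notice, but it does not say that they will be reported as safety results. It does not assure capture of unlisted, non-severe events in participants who keep attending.

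The size of any loss cannot be estimated from the protocol. What can be stated is that described open inquiry ranges from none, at full attendance, to 7 contacts at the adherence threshold, assuming one call per missed session. Whether this would bias the comparison depends on attendance differing between arms, which is unknown.

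The conclusion rests on the article's own text and not on missing forms. If a fuller protocol already asks about adverse events at each session and reports them by arm, what remains is to bring the article's sections into agreement.

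**What to change.** Reconcile the objectives in the Background, the outcome list, the Harms section, the discontinuation section and the retention section, as follows:

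- Name safety as a descriptive secondary outcome: all adverse events regardless of attribution, including the events in the discontinuation section, falls and musculoskeletal injury.
- Ask the same open question at every supervised session in both arms, and keep the missed-session call.
- Tabulate events by arm for all randomised patients, including the event that led to any discontinuation.
- Since recruitment began in October 2017, state which participants were followed under the revised question.

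The cost is one line on the session form and one table. No additional visit or staff is needed, because sessions are already supervised. The change concerns recording and reporting only, and leaves the discontinuation and interruption rules as they are. It does not ask for follow-up after participation ends, which would cost more. It also does not make the trial large enough for a formal safety comparison.
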